### Randomization and blinding

2.6

A statistician who does not participate in this trial will perform randomization. Random codes will be generated by SAS software using stratified block randomization. Randomization numbers will be assigned by the data analysis system for the Interactive Web Response System (DAS for IWRS).

Drug blinding will be performed by personnel from the statistical unit. A packer unrelated to the study will repackage IFN and placebo according to the drug packaging number, verification code, and the corresponding group generated by the SAS software. The investigational drug for each participant is packaged separately. The blinding process will be recorded and preserved.

All the individuals involved in the trial will be blinded to the treatment assignment until the end of the study. This study will be unblinded after the data-auditing report is completed, and the database is locked. The unblinded document will be signed jointly by the main researchers and statisticians.

Emergency letters shall be provided for emergency unblinding, and each random number corresponds to an emergency letter. If researchers consider that blinding hinders the management of AEs, emergency unblinding will be allowed.

## Intervention

3

Participants will receive four injections into the foramen in 2 weeks according to group allocation. The injection drugs for the treatment group include 30 μg (1 mL) IFN-α1b, 50 mg lidocaine, and 2 mL physiological saline, while the control group will be treated with 30 μg placebo (1 mL), 50 mg lidocaine, and 2 mL physiological saline. The placebo is a solvent for IFN, and its packaging and appearance are consistent with those of the experimental drug. IFN-α1b injection and placebo are both produced by Sanyuan Gene Pharmaceutical Co., Ltd., Beijing, China. Every subject will be administered 150 mg of pregabalin twice daily as part of conventional therapy.

## Procedure

4

After obtaining written informed consent, the patient will be placed in a prone position. Intervertebral foramen puncture will be performed under ultrasound guidance. After properly marking the patient and disinfecting the skin, a convex probe with a sterile cover will be placed vertically against the skin surface. Taking the injection of the thoracic intervertebral foramina as an example, the ultrasound probe is moved cephalad or caudad in a sagittal position to visualize continuous ribs. Starting from the cephalad side, the first hypoechoic area is the first rib. The probe is then moved caudally to place the target rib at the center of view. The probe is flipped 90° clockwise and slightly translated toward the thoracic vertebrae, wherein the transverse process, ribs, and pleura are visible. Subsequently, the probe is moved caudally, and the transverse process and ribs disappear, while a hyperechoic shadow formed by the inferior articular process appears. The puncture point is between the echo line of the inferior articular process and the horizontal extension of the pleura. After fixing the probe, the puncture should be performed using an in-plane approach. The needle is slowly advanced toward the target. If no blood is drawn back, the medicine is then injected.

### Concomitant treatment

4.1

Permissible combination therapy include:

Oral tramadol can be administered when the VAS score of the subject decreases by <30% after receiving two intervertebral foramen injections compared to that before treatment.Oral antipyretic drugs can be taken if the body temperature is >38.5°C.Drugs for other diseases should be taken in the same dosage during the trial.

Disallowed concomitant treatments include:

Antiviral drugs, such as acyclovir and brivudine.Local therapy such as lidocaine patches and capsaicin.Other immune modulators such as thymosin and poly IC.Taking tramadol or other opioid drugs on one’s own.Antiepileptic drugs.Other minimally invasive interventions, neuromodulation, acupuncture, and ozone injection.

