### Sample size

2.2

A preliminary study with a small sample size and ≥ 25% reduction in VAS after one treatment as the primary outcome showed that the response rate was 46% in the treatment group and 23% in the control group. With *α* = 0.05 (bilateral) and power = 0.90, PASS17 software suggested that at least 85 subjects should be included in each group. Assuming a loss to follow-up rate of 15%, the adjusted sample size should be 100.

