### Drop-out criteria

2.5

During this trial, subjects experiencing the following conditions will be considered as dropout cases, and the reason and date of dropout will be recorded in a case report form.

Self-administration of drugs that affects the trial.Occurrence of adverse events (AEs) or severe adverse events (SAEs), which makes it inadvisable to continue considering the subjects’ interests.Abnormal blood routine changes (platelets <30 × 10^9^/L, neutrophil count <0.5 × 10^9^/L) during the administration of intervertebral foramen injections, leading the researchers to determine that further participation would pose a greater risk than benefit to the subjects.A participant requests to withdraw consent.A participant is lost to follow-up.The researchers consider that further participation will be inappropriate.

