### Rescue medication

4.2

If the subjects are unable to withstand the pain and require analgesics, tramadol (100 mg) will be permitted as rescue medication. The patients are required to record the dosage and date of taking tramadol in a diary.

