### Primary outcome

5.1

The VAS score and duration of pain relief will be evaluated during the entire study period as primary outcomes (Table 1). All the patients will be required to maintain a pain diary every day. The VAS is a 100 mm continuous horizontal line with the 0 mm end indicating no pain and the 100 mm end representing the most severe pain. The duration of pain relief refers to the number of days when the pain relief rate (PRR) is ≥25%. The PRR is equal to the difference between the daily VAS score after treatment and the pretreatment VAS score divided by the pretreatment VAS score.

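### Days of relief obtained with tramadol count towards the primary relief-day outcome, and the plan does not secure follow-up of patients who self-medicate

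*Protocol article*

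**What the plan says.** All references are to the protocol article.

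- **Tramadol, first route (Section 4.1).** "Oral tramadol can be administered when the VAS score of the subject decreases by <30% after receiving two intervertebral foramen injections", compared with before treatment.
- **Tramadol, second route (Section 4.2).** "If the subjects are unable to withstand the pain and require analgesics", tramadol is permitted as rescue. No VAS threshold or time point is given. Patients note dose and date in a diary.
- **Disallowed use (Section 4.1).** Tramadol or other opioids taken on the patient's own initiative are on the disallowed list.
- **Dropout (Section 2.5).** The first criterion is "Self-administration of drugs that affects the trial". The reason and date of dropout are recorded. The section does not say whether the diary and visits go on.
- **Primary outcomes (Section 5.1).** These are VAS and duration of relief over the whole study. "The duration of pain relief refers to the number of days when the pain relief rate (PRR) is ≥25"%. Days on tramadol are not mentioned.
- **Rescue consumption (Section 5.2.3).** It is checked at each visit as a separate secondary outcome.
- **Analysis (Section 8).** The FAS is patients randomized and treated at least once. The PPS is those who complete all protocol steps. The group comparisons do not refer to rescue use.

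**The concern.** Access to tramadol depends on a post-randomization value of the pain score, and the relief that tramadol gives is then credited to the randomized treatment. If the injection works, fewer interferon patients than controls will meet the trigger, so borrowed relief days fall more often in the control arm and the measured difference shrinks. The trial could then miss or understate a real effect on one of its two primary outcomes.

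The dropout rule acts on the same kind of patient. Someone in enough pain to self-medicate becomes a dropout, and if diary entries stop at that point, the missing days come selectively from patients with poor relief. Sections 4.1 and 4.2 do not refer to each other and do not say who authorizes rescue. The same diary-recorded tablet could therefore be classed as permitted rescue at one site and as self-use leading to dropout at another.

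**Working it through.** **1. The plan's own figure.** Section 2.2 takes α = "0.05 (bilateral) and power = 0.90", and says that "the response rate was 46% in the treatment group and 23% in the control group". Response there means a VAS reduction of at least 25% after one treatment. The unpooled two-proportion formula gives

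n = [0.46×0.54 + 0.23×0.77] × (1.960 + 1.282)² / 0.23² = 0.4255 × 10.507 / 0.0529 = 84.5, so 85 per group.

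85 / 0.85 = 100 per group after 15% loss. Both stated figures reproduce, so the sample-size arithmetic is not at issue. (A pooled-variance formula gives 88. Pooled power is 0.89 at 85 and 0.93 at 100 per group.)

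**2. Who would qualify for tramadol.** The documents give no rate for a VAS fall below 30% after two injections. The pilot rates are the nearest proxy:

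- interferon: 1 − 0.46 = 54% miss 25% relief
- control: 1 − 0.23 = 77% miss it
- gap: 23 percentage points. Controls make up 77/131 = 59% of those eligible.

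**3. Dilution in relief days.** Let u be the share of eligible patients who use tramadol and D the days of use. Assume that tramadol produces relief on half of those days. Then

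shrinkage = 0.23 × u × 0.5 × D.

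- u = 0.3, D = 30: 0.23 × 0.3 × 0.5 × 30 = 1.0 day
- u = 0.7, D = 90: 0.23 × 0.7 × 0.5 × 90 = 7.2 days

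Uptake, the one-half and the range of D are assumptions. So are equal uptake among eligible patients in both arms, and that none of these days would otherwise have been relief days.

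**4. The same mechanism on the responder scale of Section 2.2 (illustration only).** If tramadol lifts a fraction f of non-responders in each arm over the 25% line, the difference becomes 0.23 × (1 − f):

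| f (assumed) | Interferon | Control | Difference (points) | Power at 100 per arm |
|---|---|---|---|---|
| 0 | 46.0% | 23.0% | 23.0 | 0.93 |
| 0.1 | 51.4% | 30.7% | 20.7 | 0.85 |
| 0.3 | 62.2% | 46.1% | 16.1 | 0.63 |
| 0.5 | 73.0% | 61.5% | 11.5 | 0.41 |

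**5. Loss of self-medicating patients.** If a fraction g of non-responders in each arm is absent from the analysis, apparent response is p / [p + (1 − p)(1 − g)]:

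- g = 0.1: 0.46/0.946 = 48.6% and 0.23/0.923 = 24.9%, difference 23.7 points
- g = 0.4: 0.46/0.784 = 58.7% and 0.23/0.692 = 33.2%, difference 25.4 points

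This pulls slightly the other way from step 4. It applies to the PPS, and to the FAS only so far as data collection actually stops.

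**The case against.** The strongest reply is that counting tramadol days is a treatment-policy question: what happens to patients assigned to interferon, rescue included. Dilution by rescue is then part of the effect and not bias. The Discussion (Section 9) leans this way, since it discourages changes to patients' medication and proposes to document them. That stands as a legitimate choice, but the article does not state it. It would also require data after self-medication to be kept, which Section 2.5 leaves open. Dilution of this kind would not by itself create a false positive, and that also stands.

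Four stronger readings are tempting, and the text does not support them:

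- **That treatment failures are deleted from the main analysis.** Anyone treated at least once stays in the FAS. Exclusion is certain only in the PPS. Loss of later data is possible but not stated.
- **That the tramadol rules flatly contradict each other.** They can be read as two permitted routes plus a ban on use outside them. The defect is ambiguity. The 30% trigger and the 25% outcome threshold serve different purposes, so it is no contradiction that a patient with 25% to just under 30% relief is both in relief and eligible for tramadol.
- **That the VAS comparison is wrong as planned.** An FAS comparison of VAS regardless of rescue is defensible. A rescue sensitivity analysis is ordinary SAP content.
- **That antipyretics bias the result in favour of interferon.** "Oral antipyretic drugs can be taken if the body temperature is" above 38.5°C, and Section 6 lists fever as a possible reaction. But the documents give no fever rate, drug class or effect on this pain. Scoring such days as non-relief could remove genuine relief days mainly from the interferon arm.

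**Conclusion.** The point holds for the relief-day outcome, on a definition that the protocol article itself fixes: days of relief obtained with tramadol count as success. If the pilot pattern persists after two injections, more controls than interferon patients would qualify, and the difference in relief days is likely diluted. The range of about 1 to 7 days illustrates the mechanism and is not an estimate. It rests on assumed uptake, effect and duration, and on a small pilot that used a different threshold and time point from the tramadol trigger.

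Selective loss of data after self-medication is a real risk that the text leaves open. It would tend to raise apparent response in both arms and slightly widen the gap, so the net direction of the two mechanisms cannot be derived from the documents. The definition and the follow-up rule should be settled before unblinding. Neither point invalidates the design.

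**What to change.** - **Sections 5.1 and 8, relief days.** State that a day with tramadol or other rescue analgesic use is not a relief day. Report the count regardless of rescue as a prespecified sensitivity analysis.
- **Section 8, VAS.** Keep the FAS comparison regardless of rescue, with a sensitivity analysis that treats rescue as failure.
- **Section 2.5, data collection.** State that diary and visit data continue after self-medication and that these patients remain in the FAS.
- **Sections 2.5, 4.1 and 4.2.** The clinical team should reconcile these so that permitted rescue and disallowed self-use can be told apart in the same way at all 11 sites. No clinical rule is proposed here.

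The cost is wording in the protocol and SAP, plus continued follow-up of patients who self-medicate. Tramadol dates are already in the diary; dates for any other analgesic would have to be recorded in the same way. The downside is that mean relief days will fall in both arms.

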### Rescue medication

4.2

If the subjects are unable to withstand the pain and require analgesics, tramadol (100 mg) will be permitted as rescue medication. The patients are required to record the dosage and date of taking tramadol in a diary.

## Outcome

5

### Primary outcome

5.1

The VAS score and duration of pain relief will be evaluated during the entire study period as primary outcomes (Table 1). All the patients will be required to maintain a pain diary every day. The VAS is a 100 mm continuous horizontal line with the 0 mm end indicating no pain and the 100 mm end representing the most severe pain. The duration of pain relief refers to the number of days when the pain relief rate (PRR) is ≥25%. The PRR is equal to the difference between the daily VAS score after treatment and the pretreatment VAS score divided by the pretreatment VAS score.

### Secondary outcome

5.2

#### Sf-36

5.2.1

The SF-36 self-administered questionnaire has 36 items and will be used to evaluate health on eight multi-item dimensions, including well-being, functional status, and general health. The SF-36 scale will be completed in six visits (Table 1).

#### Laboratory tests

5.2.2

Laboratory tests include detection and quantification of interleukin (IL)-6, IL-8, neuron-specific enolase (NSE), and S100β in the peripheral blood and VZV DNA in the peripheral blood mononuclear cells (PBMCs).

During the screening period and at the end of the fourth injection, peripheral blood samples will be collected from the subjects in disposable blood collection tubes containing ethylenediaminetetraacetic acid (EDTA) under sterile conditions. Virological test for VZV DNA in PBMCs shall be performed using polymerase chain reaction (PCR). Serological tests of IL-6, IL-8, NSE, and S100β can be done using enzyme-linked immunosorbent assay (ELISA).

#### Consumption of rescue medication

5.2.3

The dosage, frequency, and duration of rescue drug intake will be checked and recorded at each visit.

## Safety evaluation

6

In this trial, vital signs, electrocardiogram (ECG), hematology tests (differential count of white blood cells, neutrophils, lymphocytes, monocytes, red blood cells, and platelets), urinalysis (PH, protein, specific gravity, red blood cell microscopy, and white blood cell microscopy), and tests for blood chemical values (creatinine, urea, albumin, total bilirubin, direct bilirubin, ALT, and AST) will be conducted before and after treatment. If AEs or SAEs occur during participation, the symptoms, onset, duration, severity, relationship to the intervention, actions taken, and outcomes will be recorded in detail. Possible adverse reactions related to the treatment include fever, vomiting, nausea, granulocytopenia, thrombocytopenia, abnormal electrocardiogram, and rash. The incidence rates of AEs and SAEs will be determined.

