### Study design and setting

2.1

This study will be a randomized, double-blind, placebo-controlled multicenter clinical trial designed to evaluate the efficacy and safety of IFN-α1b injection into the foramen in patients with PHN. This study will be performed at 11 hospitals in China: China-Japan Friendship Hospital, First Affiliated Hospital of Chongqing Medical University, CR & WISCO General Hospital, Second Affiliated Hospital of Guangzhou Medical University, First Hospital of Lanzhou University, First Affiliated Hospital of Xiamen University, Affiliated Hospital of Xuzhou Medical University, Yanbian University Hospital, Nanjing Drum Tower Hospital, Jilin Provincial People’s Hospital, and Gansu Provincial Hospital. Two-hundred participants who meet the inclusion criteria but not the exclusion criteria will be randomly divided into treatment and control groups in a 1:1 ratio. The study will include a baseline period, a 2-week treatment, and a 3-month follow-up after enrollment. Individual researchers will screen subjects who meet the inclusion criteria. Subjects who do not meet the exclusion criteria will be included in this study. Collection of baseline information will be completed through case report form (CRF) during the baseline period. The experimental flowchart is shown in Figure 1 by Figdraw. The schedules for enrollment, intervention, and assessment are listed in Table 1.

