**Figure 1 fig1:**
[figure not shown]
Flowchart of the experimental: efficacy and safety of ultrasound-guided injection of interferon-alpha1b (IFN-alpha1b) into foramen of patients with postherpetic neuralgia.

**Table 1 tab1:** Schedule of enrolment, treatments, and assessments.

Procedure	Screening period	Treatment period		Follow-up period		
	Visit 1	Visit 2	Visit 3	Visit 4	Visit 5	Visit 6
	Day −3 to 0	Day 7 (After 2 treatments)	Day 14 (After 4 treatments)	Day 30 after treatment	Day 60 after treatment	Day 90 after treatment
Enrolment						
Informed consent	•					
Demographic information	•					
Vital sign	•	•	•	•	•	•
Physical examination	•	•	•	•	•	•
Imaging test	•					
ECG	•					
Laboratory test	•		•			
Randomization	•					
Intervention						
Treatment group		Inject interferon into intervertebral foramen 2 times per week				
Control group		placebo interferon into intervertebral foramen 2 times per week				
Assessment						
VAS	•	•	•	•	•	•
Duration of pain relief	•	•	•	•	•	•
SF-36	•	•	•	•	•	•
Virus load of VZV DNA	•		•			
humoral cytokine level	•		•			
Drug consumption	•	•	•	•	•	•
Adverse events		•	•	•	•	•

ECG, electrocardiogram; VAS, visual analogue scale; SF-36, 36-item short-form; VZV, varicella-zoster virus. Indicate completion or inclusion of the content.

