## Statistical analysis

8

An independent statistician will perform the full analysis set (FAS), per protocol set (PPS), and safety analysis set (SS). FAS is used to analyze data collected from patients randomized in the trial and treated at least once. PPS is performed in cases that complete all steps of the experimental protocol. SS is performed to analyze the data collected from subjects who receive at least one treatment and have a record of safety indicators. The number of cases in the SS will be determined as the denominator to calculate the incidence of AEs and SAEs.

Descriptive statistical results will be shown as mean ± standard deviation for continuous data, and as numbers and percentages for categorical data. Chi-square or Fisher’s exact tests shall be used for categorical data and independent t-tests or rank-sum tests for continuous data, depending on whether the data meet the normal distribution and homogeneity of variance. *p* < 0.05 will be considered to indicate a statistically significant difference.

For safety evaluation, the proportions of AEs and SAEs will be calculated using chi-square or Fisher’s exact tests. We will perform a paired t-test or rank-sum test to compare differences in vital signs and laboratory test results during the screening period and at the end of the intervention.

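### Section 6 promises an ECG both before and after treatment, but Table 1 schedules one at screening only

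*Protocol article*

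**What the plan says.** Section 6 (Safety evaluation) puts vital signs, ECG, hematology, urinalysis and blood chemistry in one sentence, beginning "In this trial, vital signs, electrocardiogram (ECG), hematology tests", and gives the whole list one timing: they "will be conducted before and after treatment". The same section anticipates ECG changes as a drug effect: "Possible adverse reactions related to the treatment include fever, vomiting, nausea, granulocytopenia, thrombocytopenia, abnormal electrocardiogram, and rash".

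Section 2.1 (Study design and setting) gives Table 1 its status: "The schedules for enrollment, intervention, and assessment are listed in Table 1". Table 1, titled "Schedule of enrolment, treatments, and assessments", has a separate ECG row. That row carries a single mark, under Visit 1 (Day −3 to 0). The cells for Visits 2 to 6 are empty.

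Section 8 (Statistical analysis) compares adverse events between groups; in its words, "the proportions of AEs and SAEs will be calculated using chi-square or" Fisher's exact tests. Its paired comparison of screening with the end of the intervention covers vital signs and laboratory results and does not name ECG.

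**The concern.** Two explicit statements about the same procedure disagree. Table 1 does not forbid a later ECG, but it omits one that Section 6 commits to. This is not detail that an article leaves to a fuller document, because no unseen protocol or analysis plan can make both statements true as printed.

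Three things are at stake:

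- **Detection.** An abnormal ECG is a reaction the protocol expects might occur. Adverse event enquiry at Visits 2 to 6 can pick up symptoms, but a symptom-free ECG change is found only by recording an ECG.
- **Uniformity.** Section 2.1 says "This study will be performed at 11 hospitals in China". A site that works from Table 1 would do no scheduled post-treatment ECG, and a site that works from Section 6 would do one.
- **The adverse event count.** An ECG abnormality recorded as an adverse event enters the proportions compared in Section 8, so part of that count could depend on which text a site followed.

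**Working it through.** The article gives no figure to reproduce. The check sets Section 6 against Table 1, row by row.

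**Inputs.** The timing comes from the first sentence of Section 6. The marks come from Table 1, Visits 1 to 6, where Visit 1 is screening and Visits 2 to 6 follow it. I take the laboratory test row to cover hematology, urinalysis and blood chemistry, since Table 1 does not list these separately.

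| Section 6 item | Marks in Table 1 | Marks after screening | Matches Section 6? |
|---|---|---|---|
| Vital signs | 6 of 6 | 5 of 5 (Visits 2–6) | yes |
| Laboratory tests | 2 of 6 | 1 of 5 (Visit 3) | yes |
| ECG | 1 of 6 | 0 of 5 | no |

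**Shortfall.** A before-and-after assessment needs at least 2 time points. Table 1 schedules 1 for ECG. The shortfall is at least 2 − 1 = 1 ECG per patient.

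**Could this come from reading the PDF?** It is unlikely. The ECG row has its full set of columns with the mark under screening, and the laboratory row directly below it kept its Visit 3 mark.

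**Does another section settle it?** No. No other section schedules a later ECG, and none limits the Section 6 sentence for ECG. Section 8 is silent on ECG: it neither plans a before-and-after comparison nor says that none will be recorded.

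**Which visit would be the post-treatment one?** Section 6 does not say. Visit 3, headed "Day 14 (After 4 treatments"), is the natural reading on two grounds: the only post-screening laboratory mark is there, and the paired comparison in Section 8 is between screening and the end of the intervention.

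**Size of the consequence.** The article gives no rate of ECG abnormality in either group, so the expected number of missed changes cannot be calculated.

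**The case against.** The mismatch itself is not in dispute. The case on the other side concerns how much it matters and which text should give way.

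- **A common case report form makes a split between sites less likely.** Section 7 has one data administrator design the form from the research plan, with verification rules and researcher approval before release. Sites would also work from the full protocol, which is not shown. This has force: a site-by-site split is a possibility, not a prediction. But the form derives from the plan, and if its source is Table 1 there may be no field for a post-treatment ECG anywhere. The detection problem would then remain, uniformly.
- **Blinding protects the comparison between groups.** Allocation is 1:1 and double-blind, so uneven ECG practice would arise without knowledge of the arm. This stands. The likely harm is under-detection in both arms and uneven recording between sites, not bias towards one treatment.
- **No planned analysis uses a post-treatment ECG.** Section 8 names only vital signs and laboratory results for the paired comparison, and Section 2.4 excludes patients with serious cardiovascular disease. Both are true and both limit the importance of the point. Neither removes the commitment in Section 6.
- **Section 6 may be the loosely worded text.** A screening-only ECG in Table 1 fits the silence of Section 8, so the article does not settle which statement was intended. This also stands, and it is why the choice of repair below rests on a judgement about safety monitoring.

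**Conclusion.** The concern holds. Section 6 and Table 1 contradict each other on ECG, and the schedule falls at least one post-treatment ECG short of what the text promises. The importance is modest: it is a safety-schedule inconsistency that should be corrected, with no effect on the efficacy analyses, the sample size or any planned test. What gives it weight is that the missing assessment is the one that would detect a reaction the protocol names in advance.

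The contradiction can be read directly from the page. The consequences rest on assumptions: that at least some sites, or the case report form, follow Table 1, and that some ECG changes would be symptom-free. Their number cannot be estimated from the article.

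**What to change.** Add an ECG mark to Table 1 at Visit 3, and state in Section 6 that the post-treatment ECG is taken at that visit. Check that the case report form has a field for it.

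Removing ECG from the Section 6 sentence would also end the contradiction, but it would leave an anticipated reaction with no planned check after dosing. Adding the mark is therefore the better choice.

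The cost is one mark in the table, a short clause in the text and at most one ECG per patient at a visit that already takes place: at most 200 × 1 = 200 recordings for the planned 200 participants. Read literally, Section 6 already commits to these. No endpoint, sample size or planned test changes.
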